### Data collection and participant follow-up

The number of patients approached, who are potentially eligible, who agree to participate, and who decline participation (with their reason for refusal) will be recorded. Once participants have provided informed consent, baseline demographics, relevant medical history, and details regarding their diagnosis will be collected from the participant, the attending surgeon, their medical record, and through physical examination. Participants will also complete the patient-reported outcome measures (PROMs) at the time of enrolment. After surgery, surgical and peri-operative details will be collected from the attending surgeon and the participant’s medical records. Adverse events occurring during the surgical procedure or perioperative period will also be documented. Post-operative radiographs will be ordered as standard of care. We will use a centralized REDCap system for all sites.

### Follow-up visits

Participants will be followed for 24 months post-surgery. Efficacy and safety outcomes will be assessed at 2 weeks, 3, 6, 12, and 24 months post-surgery at regularly scheduled clinic visits. At each time point, participants will complete the PROMs. Physical examination will be performed at 2 weeks, 3, 6, 12, and 24 months post-surgery follow-ups. Shoulder-related adverse events and serious adverse events will also be documented. In cases where the participant does not return to the clinic, study personnel will contact the participant by telephone, text, email, or standard mail. A missed follow-up form should be completed if the participant misses the follow-up visit. The schedule of events (Table 1) details the requirements and procedures for each visit.

**Table 1 Tab1:** Schedule of events

Assessment/procedures	Visit 1: Enrollment/screening	Visit 2: Surgery	Visit 3: 2 weeks post-surgery (± 7 days)	Visit 4: 3 months post-surgery (± 14 days)	Visit 5: 6 months post-surgery (± 30 days)	Visit 6: 12 months post-surgery (± 30 days)	Visit 7 24 months post-surgery (± 60 days)
Eligibility screening	●						
Informed consent	●						
Collection of demographic, medical history, radiograph	●						
Collection of surgical data		●					
Surgery		●					
WOSI	●		●	●	●	●	●
ASES	●		●	●	●	●	●
Shoulder Activity Scale	●		●	●	●	●	●
EQ-5D	●		●	●	●	●	●
Patient Satisfaction Scale	●		●	●	●	●	●
Physical examination	●		●	●	●	●	●
Radiograph (standard of care, **Latarjet only**)			●				
Follow-up form			●	●	●	●	●
Safety assessment		●	●	●	●	●	●

### Early withdrawal

Participants may decide to withdraw from this trial at any time. If a participant withdraws prior to completing the trial, the study personnel will document the reason for withdrawal and attempt to collect any available outcome data. Participants will not be withdrawn from the study due to lack of adherence to the study protocol (e.g. participant received wrong treatment arm, missed follow-up visits etc.).

### Participant retention

Once a patient is enrolled in the trial, the clinical site will make every reasonable effort to follow the participant for the entire duration of the study period. The past follow-up rates for similar fracture trials performed by the study investigators [36–38] is greater than 90%. Strategies to maintain participant retention include the following: Individuals will be excluded if they are likely to present problems with follow-up (refer to exclusion criteria). At the time of randomization, each participant will provide the name and address of their primary care physician, and the name, address, and phone number of three people at different addresses with whom the participant does not live with who are likely to be aware of the participant’s whereabouts as well as their own address and phone number. The research coordinator will confirm that these numbers are accurate prior to the participant’s discharge from the hospital. Whenever possible, participants will be given information regarding surgical stabilization for recurrent dislocations, potential complications, and benefits and will be encouraged to adhere to follow-up visits and research protocols. The study coordinator will remind participants of upcoming clinic visits. The study coordinator will contact participants no less than once every three months to maintain contact and obtain information about any planned change in residence. Efforts will be made to contact patients to ensure follow-up compliance and that appointment reminders will be conducted by both fracture clinic and study staff to ensure compliance. Because the STABLE study will be a younger population who may be less likely to attend follow-up visits compared to older fracture populations, it is possible that follow-up rates will not be as high as our group’s previous studies, which is a key reason to conduct this pilot trial. We will use the information from this pilot study to refine our participant retention strategies for the definitive trial.

### Trial committees

The Steering Committee will provide guidance and direction; specific responsibilities include reviewing and approving the study protocol and working collaboratively to resolve any challenges that arise during the pilot study. The Steering Committee will be comprised of national and international experts in shoulder and orthopaedic surgery and research methodology. The committee will be blinded throughout the trial. Data and Safety Monitoring Committee (DSMCs) are generally recommended for any controlled trial that will compare rates of mortality or major morbidity. Guidance from the Federal Drug Administration supports that a DSMC is not needed for clinical trials exploring interventions to promote symptom relief (http://www.fda.gov/RegulatoryInformation/Guidances/ucm12069.html). As such, a DSMC will not be used in the pilot trial.

## Statistical plan

### Sample size

The feasibility objectives in our pilot study do not lend themselves to traditional quantitative sample size calculations. If we use CIs limits for the binary outcome of compliance or not at 80% with a CI of 20%, we require 70 patients total. If we account for 15% loss to follow-up, we require a total of 82 patients. Therefore, we propose a sample size of at least 82 participants (41 participants per treatment arm). We have used similar pilot sample sizes to demonstrate feasibility in our previous multi-centre trials [36–39].

### Analysis plan

#### Primary analysis—Feasibility

To meet the feasibility objectives of this pilot randomized controlled trial we have planned descriptive analyses. We will present point estimates of recruitment and feasibility events, including adherence to protocol, follow-up rate at 24 months, and data completeness as proportions with 95% CIs. The pilot study results will be evaluated to identify recruitment issues and data management issues and inform anticipated follow-up rates.

#### Secondary analysis

All outcome analyses will be exploratory only and will adhere to the intention-to-treat principle. For the pilot study, we will perform summary descriptive analyses for recurrence rate and for all clinical outcome measures. This will include measures of central tendency (mean, median) and variance (95% CI, standard deviation, inter-quartile range), or proportions/risks (e.g. RR, odds ratio) where appropriate. Because the pilot trial is not powered to detect differences in clinical outcomes, we will not present *p* values. We will present all point estimates with 95% confidence intervals and graphically overlay minimally important differences (MIDs) to give context.

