### Randomization

To ensure concealed allocation, eligible patients will be randomized using a centralized online randomization system within the Research Electronic Data Capture (REDCap) system. We will use an allocation ratio of 1:1. We will use random block sizes of 4 and 6, and we will stratify by clinical site. A data manager generated the randomization sequence and is the only team member with access to the sequence. Site research personnel will randomize patients.

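### PROM comparisons are planned only as descriptive summaries although every score is collected at enrolment; baseline adjustment would probably narrow the intervals set against the MIDs, at almost no cost

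*Protocol article*

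**What the plan says.** The protocol article, under Secondary analysis, sets one approach for every clinical outcome: "we will perform summary descriptive analyses for recurrence rate and for all clinical outcome measures". For continuous measures it lists "measures of central tendency (mean, median) and variance (95% CI, standard deviation, inter-quartile range"; for binary outcomes it also mentions risk ratios and odds ratios. The status is plain: "All outcome analyses will be exploratory only and will adhere to the intention-to-treat principle". No p values will be shown because "the pilot trial is not powered to detect differences in clinical outcomes". Point estimates will carry 95% confidence intervals, and the authors will "graphically overlay minimally important differences (MIDs) to give context".

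Two other sections bear on this. Data collection and participant follow-up states: "Participants will also complete the patient-reported outcome measures (PROMs) at the time of enrolment". Table 1 confirms that WOSI, ASES, Shoulder Activity Scale and EQ-5D are each taken at enrolment and at every post-operative visit. The Randomization section states: "We will use random block sizes of 4 and 6, and we will stratify by clinical site".

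The article names no covariate, change score or stratum term. It does not use the word unadjusted, and it does not define how a between-arm difference in a continuous score will be estimated.

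**The concern.** The Objectives section says the two procedures will be compared on function and quality of life. With no p values, the interval set against the MID is what a reader will take from the PROM data. The statistics listed for continuous scores describe one group at a time. A reader who follows the text literally would therefore either compare per-arm intervals, which do not show the uncertainty of the difference, or take a raw difference in follow-up means.

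A raw difference makes no use of the enrolment score. With about 35 completers per arm, chance imbalance in baseline scores can be noticeable, and the part of the outcome variance that baseline predicts stays in the interval. What is at stake is precision, and how informative the MID display is. The Objectives section says the clinical objectives of the pilot will be those of the definitive trial, so a baseline-adjusted residual SD would also be useful if that trial analysed a PROM with such a model.

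**Working it through.** **Inputs from the article.** The Sample size section gives 82 participants, 41 per arm. The Primary outcome section sets 70 of 82 with complete two-year follow-up, so 70/2 = 35 per arm, and refers to 10 active sites. Allocation is 1:1, stratified by site.

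**The plan's own figure.** No width is stated for any PROM interval, so there is none to reproduce. The sample size rests on a feasibility proportion. An exact 95% interval for 80% has total width 0.199 at n = 70, and 70/0.85 = 82.4 against the stated 82. The point here leaves that figure untouched.

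**Assumptions.** The article gives no baseline-to-24-month correlation r, no outcome SD and no between-site intraclass correlation (ICC). Widths are therefore in units of the outcome SD, and r and ICC are varied.

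**Step 1: unadjusted difference, n = 35 per arm.**
Half-width = t(0.975; 2n-2) × √(2/n) = 1.9955 × 0.2390 = 0.477 SD.

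**Step 2: analysis of covariance on the baseline score.**
Half-width = t(0.975; 2n-3) × √(2/n) × √(1 + 1/(2n-4)) × √(1 - r²) = 1.9960 × 0.2390 × 1.0075 × √(1 - r²) = 0.481 × √(1 - r²) SD.
The lost degree of freedom and the third factor are the price of estimating the slope and allowing for chance baseline imbalance.

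| r | adjusted half-width (SD) | ratio to 0.477 | change in width |
|---|---|---|---|
| 0 | 0.481 | 1.008 | about +1% |
| 0.2 | 0.471 | 0.987 | about -1% |
| 0.3 | 0.459 | 0.961 | about -4% |
| 0.5 | 0.416 | 0.873 | about -13% |
| 0.7 | 0.343 | 0.720 | about -28% |

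**Step 3: break-even.** The ratio equals 1 when 1.0078 × √(1 - r²) = 1, so r² = 1 - 1/1.0078² = 0.0155 and r is about 0.124.

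**Step 4: all 41 per arm followed.** The unadjusted half-width is 0.440 SD. The ratios are nearly the same: 0.960, 0.872 and 0.719 at r = 0.3, 0.5 and 0.7.

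**Step 5: site.**
- Site alone (10 sites, arms balanced within site): ratio = t(0.975; 59)/t(0.975; 68) × √(1 - ICC) = (2.0010/1.9955) × √(1 - ICC). This is 1.003 at ICC 0, 0.977 at ICC 0.05 and 0.951 at ICC 0.10.
- Baseline plus nine fixed site indicators, ICC 0, without exact balance within sites: the ratio is 1.037 at r = 0.3, 0.997 at r = 0.4 and 0.942 at r = 0.5. Each is worse than adjusting for baseline alone.

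The worthwhile gain comes from the baseline score. Site adds a few percent at most over this range, and fixed site indicators can cost precision.

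**The case against.** The strongest reply is that the article never says the comparisons will be unadjusted. The listed statistics describe distributions and do not define a between-arm estimator; covariates and model form are commonly left to an analysis plan, which is not shown here. This stands as far as it goes: unadjusted is the natural reading of a plan for descriptive summaries, not the plan's own word. It does not remove the point, because the article does state a method covering all clinical outcomes, and a model-based difference would go beyond what it describes.

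Second, the outcomes are exploratory, the MIDs are there for context, and the three feasibility thresholds (recruitment, crossovers, follow-up) use no PROM interval. This stands in full and limits the priority.

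Third, under randomization an unadjusted difference is unbiased, and its interval already allows for chance baseline imbalance. Leaving out site makes the interval, if anything, conservative. This also stands.

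A reader might infer more: that the planned intervals are certainly wider than the data allow, that adjustment is entirely free in precision, or that ignoring site is itself a fault. The documents support none of these. The gain depends on an r they do not give and vanishes below about 0.12; at r = 0 adjustment costs just under 1% of width; and the site term has little effect over the range examined.

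**Conclusion.** The point holds as a low-severity improvement, not as an error in the plan. The analysis as described, naturally read as unadjusted, gives valid PROM intervals that are probably wider than necessary, given that all four scores are already collected at enrolment. The gain and loss are lopsided. At 35 per arm the worst case is about 1% wider (r = 0), against about 4%, 13% and 28% narrower at r = 0.3, 0.5 and 0.7.

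This rests on about 35 completers per arm, a linear relation between baseline and 24-month score with a common SD in both arms, and an assumed r. Recruitment, crossover and follow-up conclusions and the sample size of 82 are unaffected.

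**What to change.** State in the Secondary analysis section (or in the analysis plan, if one exists and does not already say so) that:

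- for each PROM, the between-arm mean difference at 24 months will be estimated with a 95% confidence interval and no p value, from a linear or repeated-measures model with arm and baseline score;
- a random site intercept will be added where it can be fitted, because allocation is stratified by site. With about 82/10, or 8, participants per site, this is preferable to fixed site indicators, and the expected gain is small;
- the MID will be overlaid on that adjusted difference, not on per-arm intervals;
- the raw per-arm summaries already planned will be kept as descriptive tables.

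Reporting the observed baseline-to-24-month correlation and the residual SD alongside would help anyone planning the definitive trial. The cost is a few sentences of text and a little more analysis work; no new data or visits are needed.

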### Interim analysis

We will not conduct an interim analysis for this pilot trial.

### Data management

#### Case report forms and data transmission

Clinical sites will be provided with the trial case report forms (CRFs) prior to initiation of enrollment. Research personnel at each clinical site will submit the required data, as detailed on the CRFs, to the Methods Centre using the REDCap system. Clinical site personnel will receive a unique login and password for the REDCap system and will be able to view and modify data for participants recruited at their clinical site.

#### Data integrity

The REDCap system uses a variety of mechanisms for checking data at the time of entry including skip logic, range checks, and data type checks. Upon receipt of new data, the personnel at the Methods Centre will query all missing, implausible, or inconsistent data, clinical site personnel will be notified of open queries through regular reports and will be required to respond promptly.

## Ethics and dissemination

This protocol has been reviewed and approved by the Hamilton Integrated Research Ethics Board (HiREB; project number 4942) and will be approved by the local Institutional Review Board (IRB) or REB of each participating clinical site prior to initiation of trial activities at the clinical site. We will seek written informed consent from each study participant.

Any amendments to the study protocol which may affect the conduct of the study, or the potential safety of or benefits to participants (e.g. changes to the study objectives, study design, sample size, or study procedures) will require a formal amendment to the protocol. Any protocol amendments will be approved by the principal investigator and will require approval by the lead site REB and the local REB/IRB at each participating clinical site. Administrative changes (e.g. minor corrections or clarifications that have no effect on the way the study is conducted) will not need to undergo a formal amendment process.

Results from the study will be submitted for publication regardless of whether or not there are statistically significant findings. Every attempt will be made to ensure that the amount of time between completion of data collection and release of study findings is minimized.

## Data Availability

Not Applicable

## Abbreviations

ASES: American Shoulder and Elbow Society
CEO: Centre for Evidence-Based Orthopaedics
CI: Confidence intervals
CONSORT: Consolidated Standards of Reporting Trials
CRF: Case report forms
CT: Computed tomography
DSMC: Data Safety Monitoring Committee
EQ-5D: EuroQol-5 Dimensions
MID: Minimally important differences
HiREB: Hamilton Integrated Research Ethics Board
IRB: Institutional Review Board
PROMs: Patient-reported outcome measures
REB: Research Ethics Board
REDCap: Research electronic data capture
RR: Risk ratio
SPIRIT: Standard Protocol Items: Recommendations for Interventional Trials
STABLE: Shoulder instability Trial comparing Arthroscopic stabilization Benefits compared with Latarjet procedure Evaluation
WOSI: Western Ontario Shoulder Instability
WSIB: Workplace Safety and Insurance Board
US: Unites States
